### Intervention

The intervention group will receive NP-led care. The initial visit is with an experienced NP with extra training in AF management. A complete baseline history and physical examination will be completed to determine a plan of care based on current CCS AF guidelines. CHADS_2_/CHA_2_DS_2_-VASc score [34] will be calculated to identify the risk of stroke for each patient. To assist with determining risk for increased potential for bleeding, the HAS-BLED score [35] will be calculated. Canadian Cardiovascular Society Severity in Atrial Fibrillation Scale scores [36] will also be calculated to identify symptom severity of AF. A cardiologist will be consulted if the patient develops heart failure; medication intolerances (which limit medical management) requiring assessment for treatment with amiodarone, electrical cardioversion, or pulmonary vein isolation; or other serious complications. The NP will also provide individualized patient education (“What is AF?,” “AF management and complications”). Patients will be given a written treatment plan at the end of the consult to assist with patient compliance, self-management, and knowledge retention. Patients will also be provided with clinic contact information for future needs.

The NP will see the patient in follow-up at 3 and 6 months; however, if the patient’s condition requires closer follow-up, timing will be adjusted and documented. The patient’s history will be reviewed to determine if the patient has been hospitalized or has had any major adverse cardiovascular events. A provincial electronic medical record will also be reviewed for prescribed medications, dates of hospitalizations and emergency room visits, laboratory blood work results (e.g., international normalized ratio, troponin, brain natriuretic peptide, hemoglobin), and diagnostic tests (echocardiograms, chest x-rays, medical consultations, computed tomographic scans, and 12-lead electrocardiogram tracings).

The control group will receive standard care by a cardiologist in the EASE Clinic. The cardiologist will determine AF management and follow-up requirements as per their usual practice. The patient’s care will be referred back to the family physician if no follow-up is required. The schedule of enrolment, intervention, and assessments of the complete study protocol (according to Additional file 1: Standard Protocol Items: Recommendations for Interventional Trials [SPIRIT] checklist) is shown in Fig. 2.

**Fig. 2 Fig2:**
[figure not shown]
Standard Protocol Items: Recommendations for Interventional Trials (SPIRIT) diagram. AFEQT Atrial Fibrillation Effect on QualiTy of life survey, CV Cardiovascular

### Outcomes

The primary outcome is the difference in change in AFEQT scores from baseline to 3 months and 6 months between the intervention and control groups. AFEQT is an AF-specific questionnaire [37] for use with patients with any type of AF. AFEQT is a simple survey with 20 questions based on a 7-point Likert scale covering 3 domains. The questionnaire should take about 5 minutes to complete. Four questions assess AF-related symptoms, eight questions evaluate daily functioning, and six questions evaluate AF treatment concerns. Two questions assessing satisfaction with treatment are not included in the overall score. Questions 1–18 are included in the overall scoring of the questionnaire. A score of zero corresponds to complete disability, whereas a score of 100 corresponds to no disability. The AFEQT has been shown to have good reliability, test-retest reliability, construct validity, and responsiveness as well as discriminatory properties between clinically different groups [37]. The lowest global score is associated with the patients with severe symptoms related to AF. The AFEQT has also been shown to be responsive to change [37].

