**Methods/design:**

We plan a randomized controlled trial comparing NP-led care vs. standard care. Inclusion criteria are ≥18 years of age, documented nonvalvular AF, willingness to give informed consent, and capacity to complete questionnaires. Patients referred for electrophysiological intervention who are clinically unstable or unable to attend follow-up visits will not be eligible to participate. Patients will be asked for verbal consent during the initial triage phone call from the nurse. Randomization will occur via a secure website. The intervention includes an NP consult, including medical history, physical examination, patient teaching, treatment plan, and follow-up at 3 and 6 months. The control arm involves usual cardiologist consultation with follow-up determined by the cardiologist’s practice pattern. The primary outcome will be the difference in change in Atrial Fibrillation Effect on Quality of Life Survey scores at 6 months between groups. Secondary outcomes will include difference in change of EQ-5D scores at 6 months between groups, difference in composite outcomes of death resulting from cardiovascular cause, hospitalizations and emergency department visits between groups, and satisfaction with NP-led care measured by the Consultant Satisfaction Questionnaire. A sample size of 70 per group will ensure adequate power despite a potential 10% loss to follow-up.

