### Sample size

A minimally important difference (MID) for change in AFEQT score was not identified in a review of the literature. In the initial validation study [37], the SD for change from baseline to 3 months in the medically managed group was 20.0 (overall AFEQT global score). This group is most like the projected population for this study, and that value was therefore used as the SD for sample size calculations. We consulted [name], an experienced arrhythmia specialist, AF QoL researcher, and coauthor of the AFEQT questionnaire, who suggested that the MID for AFEQT is 12. As such, we chose an effect size of 12 (i.e., NP-led care would improve AFEQT scores by at least 12). A sample size of 64 participants in each group will detect an MID of 12 in AFEQT scores (SD 20, two-tailed *t* test, 80% power, and significance level of 5%). Seventy patients per group (total 140) will be recruited to allow for 10% loss to follow-up.

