All sociodemographic and clinical characteristics for the intervention (NP-led care) and control groups at baseline will be summarized using mean ± SD for continuous variables and the observed counts and percentages for categorical variables. For the main outcome, analysis of covariance (ANCOVA) will be used to assess change in AFEQT scores over time: baseline to 3 months and 3 months to 6 months (repeated dependent measures) in both the intervention and control groups. ANCOVA assumes normal distribution of the data as well as homogeneity of variance and the groups being balanced. Adjustment for pretest scores will identify whether the postintervention difference in scores is truly a result of the intervention. ANCOVA will also account for variation around the posttest means that comes from the variation attributed to the patients AFEQT scores started at baseline. Previously, it has been shown with other HRQoL scores that data can be skewed because of ceiling or floor effects resulting from extreme values and unequal distances between values on ordinal scales [40]. However, the central limit theorem states that the means will be normally distributed regardless of the original distribution when there are at least 30 per group [41]. This study is projected to have 2 equal groups with 70 participants. If the initial data analysis reveals nonnormal distributions and skewed data, further analysis will be completed to determine if transformation of the data is required or if other statistical analysis would be more appropriate. An independent *t* test will be used to assess the difference in means between NP care and physician-led care. Kaplan-Meier survival analysis will be used to evaluate the composite endpoint of cardiovascular death and hospitalizations determined by blinded assessors. Multivariate analysis will be used to adjust for possible differences in baseline characteristics and scores for any significant variables. Consultant satisfaction will be determined by comparing the means with independent *t* tests. A *p* value less than 0.05 will be considered statistically significant. All analyses will be based on the intention-to-treat principle.

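### The primary AFEQT outcome is defined at 6 months in the abstract, at 3 and 6 months in Outcomes, and over different intervals again in the analysis text

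*Protocol article*

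**What the plan says.** The protocol article describes the primary comparison in four places.

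- **Abstract, Methods/design:** "The primary outcome will be the difference in change in Atrial Fibrillation Effect on Quality of Life Survey scores at 6 months between groups". This is one time point.
- **Outcomes:** "The primary outcome is the difference in change in AFEQT scores from baseline to 3 months and 6 months". This is two time points.
- **Analysis paragraph (under the Sample size heading):** ANCOVA of AFEQT over "baseline to 3 months and 3 months to 6 months (repeated dependent measures) in both the intervention and control groups". The second interval, 3 to 6 months, appears in neither definition above. The paragraph then adds: "An independent *t* test will be used to assess the difference in means between NP care and physician-led care", with no time point. One general threshold follows: "A *p* value less than 0.05 will be considered statistically significant".
- **Sample size:** a single comparison of 12 points ("SD 20, two-tailed *t* test, 80% power, and significance level of 5"%), giving 64 per group and 70 recruited. The SD is taken from 3-month data: "the SD for change from baseline to 3 months in the medically managed group was 20.0".

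By contrast, the secondary outcomes each name one visit where a visit applies: EQ-5D change to 6 months and the satisfaction questionnaire at 6 months.

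**The concern.** A superiority trial needs one stated contrast, or one stated rule for combining contrasts, that decides success. Here the abstract and the Outcomes section are both current text and they disagree. The analysis paragraph agrees with neither.

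As written, a result that is significant only at 6 months can be presented as primary success by citing the abstract. One that is significant only at 3 months can be presented as primary success by citing Outcomes. If the choice is made after the data are seen, the nominal 5% no longer describes the error rate, and a reader cannot tell a planned claim from a selected one.

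The 3-to-6-month interval adds a different difficulty. If NP-led care produced the full 12-point difference by 3 months and held it at 6 months, the group difference in the 3-to-6-month change would be 12 − 12 = 0. A sustained benefit would look null on that contrast.

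**Working it through.** **1. The definitions side by side**

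| Place | AFEQT contrast |
|---|---|
| Abstract | change at 6 months |
| Outcomes | change from baseline to 3 months and 6 months |
| Analysis paragraph, ANCOVA | baseline to 3 months; 3 to 6 months |
| Analysis paragraph, t test | not stated |
| Sample size | one comparison; SD from 3-month change |

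The two-visit wording in Outcomes is unlikely to be shorthand for 6 months, because the secondary outcomes show that the authors name a single visit when they mean one.

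**2. The plan's own figure**

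Inputs (Sample size): difference 12, SD 20, two-sided 5%, 80% power.

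n per group = 2 × (1.960 + 0.842)² / (12/20)² = 2 × 7.849 / 0.36 = 43.6, so 44 (45 with the t distribution).

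The stated 64 does not reproduce. It matches a standardised difference of 0.5: 2 × 7.849 / 0.25 = 62.8, so 63 (64 with the t distribution). That is a separate matter. What counts here is that the calculation covers one comparison at 5%, and that at 64 per group the power on the stated inputs is about 92%.

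**3. Type I error if either time point were enough**

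Take two two-sided tests at 0.05 with critical value 1.96 and jointly normal statistics with correlation r. The article gives no r, so r is an assumption.

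P(at least one false positive) = 1 − P(|Z₁| < 1.96 and |Z₂| < 1.96)

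| r | Type I error |
|---|---|
| 0 | 1 − 0.95² = 9.75% |
| 0.5 | 9.1% |
| 0.6 | 8.8% |
| 0.7 | 8.3% |
| 0.8 | 7.8% |
| 0.9 | 7.0% |

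The two contrasts share patients and baseline scores, so a positive r is expected and 9.75% is a ceiling.

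**4. If both time points were required**

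The type I error cannot exceed 5%, because each test alone is held at 5%.

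For power, take 12 points and SD 20 at both visits and 70 × 0.9 = 63 per group. The mean of each statistic is 0.6 × √(63/2) = 3.37.

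- One test: Φ(3.37 − 1.96) = 92.0%.
- Both significant: 0.920² = 84.7% at r = 0; 86.4% at r = 0.5; 87.0% at r = 0.6; 87.6% at r = 0.7.

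All of these exceed the planned 80%.

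**5. If one overall group test were used**

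A repeated-measures ANCOVA giving a single group effect across visits is one test at 5%, so there is no inflation.

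**The case against.** The strongest reply is that the inconsistency is real but its harm can be overstated. Four parts of that reply need an answer.

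- **Two chances to win.** A reader might infer that 3 and 6 months are each tested at p < 0.05 and that either suffices. The article does not say this. It gives one general threshold, and its mention of repeated measures could mean a single overall test. This objection stands, and the figures in step 3 are conditional on that reading.
- **Lost power.** A reader might also infer that requiring both visits would leave the trial underpowered. On the stated inputs it would not: power is 86% to 88% for r of 0.5 to 0.7, against a plan of 80%. The fall is from the recalculated 92%, which was never the planned value. This objection stands too.
- **Multiplicity belongs in the SAP.** An alpha split or testing order is commonly set there, and the SAP is not shown. Its absence from the article is not a fault, and the point does not rest on it. However, any SAP rule would still conflict with the abstract or with Outcomes.
- **An abstract condenses.** Condensing can drop detail, but dropping one of two primary time points changes the definition. Appeal to brevity also does not explain the analysis paragraph's 3-to-6-month interval.

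**Conclusion.** The point holds as an internal contradiction about the primary time point, across the abstract, Outcomes and the analysis paragraph. No passage resolves it, and the sample size assumes a single 5% comparison.

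The size depends on the reading. Under an either-visit rule at 0.05 each, the type I error would be about 7.8% to 9.1% for an assumed correlation of 0.8 to 0.5, and no more than 9.75%. Under a both-visits rule or one overall test, 5% is held. The power figures for the both-visits rule assume the stated 12 points and SD 20 at each visit with 63 per group.

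The documents do not establish that the trial's error rate is inflated. They leave open several ways of claiming success, only some of which hold 5%. Because this concerns the outcome that decides the trial and is cheap to settle, it should be corrected. The article reports 31 of 140 patients enrolled at the time of writing, so the choice could still be fixed well before final data.

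**What to change.** - **Outcomes:** state that the sole primary outcome is the between-group difference in AFEQT change from baseline to 6 months, as in the abstract. List the 3-month contrast as secondary.
- **Analysis paragraph:** name the primary test as the ANCOVA group contrast at 6 months, adjusted for baseline AFEQT. The baseline adjustment comes from this paragraph, not from the abstract. Remove the 3-to-6-month interval from the primary analysis or label it secondary. Give the t test a time point and a supportive role.
- **Sample size:** say that the SD of 20, taken from 3-month change, is assumed to apply at 6 months.

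No visit, questionnaire or recruitment target changes. An effect seen only at 3 months would no longer count as primary success. The Ethical considerations section sends any protocol modification back to the ethics board, so this one must go there.

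If the sponsor prefers to keep both visits primary with success at either, testing each at 0.025 holds the overall error at or below 5%. On the stated inputs that needs 2 × (2.241 + 0.842)² / 0.36 = 52.8, so 53 per group (55 with the t distribution), and the planned 64 gives about 87% power per visit. If the 64 really rests on a difference of 10 with SD 20, the need becomes 78 per group and 64 gives about 71%. Naming 6 months alone avoids that dependence.

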### Secondary outcomes include

*Difference in change in EQ-5D from baseline to 6 months between intervention and control groups*: The EQ-5D is a simple five-question general QoL questionnaire. It assesses five dimensions of QoL: mobility, self-care, usual activities, pain/discomfort, and anxiety/depression. It also has a visual analogue scale on which patients self-rate their overall health. A utility of 1 represents full health, whereas a utility of zero represents a state equivalent to death [38].
*Difference in composite outcomes of death from cardiovascular causes, cardiovascular hospitalization, and emergency room visits between the intervention and control groups (for ischemic stroke, heart failure, acute myocardial infarction, systemic embolism, major bleeding, severe arrhythmic events, and life-threatening adverse effects of drugs)*: [name] will chair a blinded committee to determine this outcome.
*Satisfaction with healthcare provider care will be assessed as measured by the overall mean score of the Consultation Satisfaction Questionnaire (CSQ) completed at the 6-month follow-up visit*: The CSQ is a self-administered tool with 18 questions using a 5-point Likert scale ranging from strongly agree to strongly disagree [39]. Three factors are considered: (a) professional aspects of the consultation, (b) depth of patient relationship, and (c) perceived length of consultation. There are three questions related to overall general satisfaction. Higher scores indicate higher satisfaction.

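### No baseline-adjusted analysis is fixed for EQ-5D: ANCOVA is tied to AFEQT, and the only unassigned between-group test is an unadjusted t test

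*Protocol article*

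**What the plan says.** Protocol article, "Secondary outcomes include" list: the first item is "Difference in change in EQ-5D from baseline to 6 months between intervention and control groups". EQ-5D is therefore measured at baseline and at follow-up, and both a utility and a visual analogue scale are described.

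The analysis methods stand under the Sample size heading and are given outcome by outcome:

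- AFEQT: "For the main outcome, analysis of covariance (ANCOVA) will be used to assess change in AFEQT scores over time". The text that follows justifies this by adjustment for pretest scores.
- No outcome named: "An independent *t* test will be used to assess the difference in means between NP care and physician-led care".
- Composite endpoint: Kaplan-Meier analysis.
- No outcome named: "Multivariate analysis will be used to adjust for possible differences in baseline characteristics and scores for any significant variables".
- CSQ: "Consultant satisfaction will be determined by comparing the means with independent *t* tests".

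EQ-5D is not mentioned in the analysis text.

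**The concern.** EQ-5D is the trial's only generic quality-of-life measure, and its baseline value has to be collected anyway to form a change. The article gives two reasons for using ANCOVA on AFEQT: it adjusts for where patients started, and it removes outcome variation that comes from baseline. Both apply equally to EQ-5D, and no reason is given for treating the two scores differently.

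As the text stands, an analyst looking for an EQ-5D method finds one unassigned test, and that test makes no use of baseline as a covariate. The one other route to adjustment is conditional on significance. Baseline EQ-5D would then enter the model or not according to the data, although its value as a covariate comes from its correlation with the outcome and not from a p value. At stake are a wider confidence interval than the collected data allow, and an estimate that moves with any chance difference between the arms at baseline.

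**Working it through.** **Plan's own figure.** There is none for EQ-5D: no SD, correlation, target difference or power. The sample size of 64 per group refers to AFEQT only. Whether that figure follows from its inputs is a separate question, and it is not used here.

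**Inputs.**
- From the article: 70 recruited per group with 10% loss, so 70 × 0.9 = 63 analysed per group; two-sided 5% level.
- Assumed: rho, the correlation between baseline and 6-month EQ-5D, from 0.3 to 0.9; the same SD (sd) at both times.

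**Variances.**
- Change score: 2(1 − rho) sd².
- ANCOVA: (1 − rho²) sd².
- Ratio, ANCOVA to change score: (1 − rho²) / [2(1 − rho)] = (1 + rho)/2.

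The direction does not depend on equal SDs. With baseline SD s0 and follow-up SD s1, the change-score variance minus the ANCOVA variance is (s0 − rho·s1)², which is never negative. Only the size of the saving depends on that assumption.

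**Power.** Take an effect that the change-score t test would detect with 80% power. In the normal approximation its expected z is 1.960 + 0.842 = 2.802. Under ANCOVA this becomes 2.802 / √[(1 + rho)/2], and power is Φ(that value − 1.960).

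| rho (assumed) | variance ratio | variance saved | SE ratio | z under ANCOVA | power |
|---|---|---|---|---|---|
| 0.3 | 0.65 | 35% | 0.806 | 3.475 | 93.5% |
| 0.5 | 0.75 | 25% | 0.866 | 3.235 | 89.9% |
| 0.7 | 0.85 | 15% | 0.922 | 3.039 | 86.0% |
| 0.9 | 0.95 | 5% | 0.975 | 2.874 | 82.0% |

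At rho 0.5, the 63 patients per group would be worth 63 / 0.75 = 84 analysed by change score, that is 21 more per group.

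**Baseline imbalance.** If the arms differ by D at baseline by chance, the change-score difference is shifted by −(1 − rho)D. At rho 0.5 and D = 0.25 SD, the shift is 0.5 × 0.25 = 0.125 SD. ANCOVA removes it. The standard error of a baseline difference at 63 per group is √(2/63) = 0.178 SD, so a difference of 0.25 SD is 0.25 / 0.178 = 1.40 standard errors. One at least that large, in either direction, is expected in about 16% of trials of this size. Averaged over randomisations the shift is zero, so this is a matter of precision and not of bias.

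**The case against.** The strongest reply is that the article does not assign the t test to EQ-5D at all. The sentence names no outcome. It follows directly on the discussion of AFEQT and of normality, and the AFEQT sample size is itself built on such a test ("SD 20, two-tailed *t* test, 80% power, and significance level of 5"%). It may therefore be a second AFEQT comparison. If so, all that remains is an unnamed method for a secondary outcome, which a condensed article may leave to an analysis plan. Much of this stands. A reader might infer that the plan prescribes an unadjusted t test for EQ-5D and never uses its baseline. The documents do not go that far: the t test is reached only by elimination, and the multivariate sentence does allow for baseline scores.

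A reader might also infer that defining the outcome as a change rules out ANCOVA. It does not. AFEQT is likewise defined as a difference in change, and it is analysed by ANCOVA.

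It might further be thought that the upper limit of the EQ-5D utility makes the problem worse. Nothing in the article supports this. Chance imbalance comes from randomisation, and the article already allows for skewed data ("further analysis will be completed to determine if transformation of the data is required or if other statistical analysis would be more appropriate").

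Finally, every figure for the gain rests on an assumed rho, and the trial is not powered on EQ-5D. Both are true.

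The reply does not remove the main point. On either reading of the t-test sentence, the article ties baseline adjustment to AFEQT and offers other outcomes only a conditional version. That is a matter of what the text fixes, not only of what it omits.

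**Conclusion.** The point holds as a minor one. The article states no unconditional baseline-adjusted analysis for EQ-5D, and the only test left unassigned is unadjusted. If EQ-5D change is analysed by that test, the comparison remains valid and unbiased but gives up precision. The saving forgone is 35% of the variance at rho 0.3, 25% at 0.5, 15% at 0.7 and 5% at 0.9, assuming equal SDs at both times. An effect with 80% power by change score would have between about 93% and 82% power by ANCOVA over that range. The gain is small if rho is high, and the documents do not say where in the range it lies. No stated power claim and no part of the AFEQT analysis is affected.

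**What to change.** Add one sentence to the analysis text before outcomes are compared by arm: 6-month EQ-5D index and visual analogue scale will each be compared between arms by ANCOVA, with arm and the baseline value of the same measure as covariates. State that baseline is included in every case, whatever its p value, and that the adjusted mean difference is reported with its 95% CI. Keep the independent t test for the CSQ, which is completed only at 6 months and has no baseline. It would also help to name the outcome to which the unassigned t-test sentence refers.

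The cost is the wording and one residual degree of freedom out of 2 × 63 − 2 = 124. Baseline EQ-5D is already collected, so no patients, visits or questionnaires are added.
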